#### SHI study population

2.3.1

The SHI population for EvaClosure is selected from the data pool of a German statutory health insurance fund that comprises over 3 million insured persons. EvaClosure uses data from the years 2015 to 2021. Patients are selected if they
are 18 years or older, andhave a diagnosis code (of the 10th revision of the International Statistical Classification of Diseases and Related Health Problems; ICD-10) for AF documented in at least two different quarters during the baseline period (I48.0, I48.1, I48.2, I48.9)Patients are excluded from the sample in case of
discontinuous data coverage (e.g., due to interrupted insurance periods or change of health insurance fund)an absolute contraindication for ASA (an ICD-10 code for gastric or duodenal ulcers (K25.- or K26.-) or a prescription for methotrexate [Codes within the Anatomical Therapeutic Chemical Classification System (ATC): L01BA01 or L04AX03])previous heart transplant (code within the German Operation and Procedure Classification System; OPS: 5–375)malignant neoplasm of the heart, mediastinum, and pleura (ICD: C38.-) orpregnancy, birth, or postpartum diagnosis in the baseline period (ICD: O–.—)Patients are assigned to the high-risk group if in the baseline period they additionally have the following characteristics:
CHA_2_DS_2_VASc-Score ≥ 2, andhigh risk for bleeding, i.e., if at least one of the following criteria are met:
○HAS-BLED value of ≥ 3, or○an ICD-10 code for other non-traumatic intracranial hemorrhage (I62.-), or○gastrointestinal bleeding (K92.2), or○hematuria (R31), or○bleeding from the respiratory tract (R04.-), or○chronic kidney disease (N18.4)From the high-risk patients, the LAAC intervention group is selected using the following inclusion criteria:
Diagnosis-related group (DRG): F95A (interventional septal occlusion, age < 18 years, or atrial appendage occlusion) andOPS code 8-837.s0 (since 2016) or 8-837.s (before 2016)The control group (best medical care group) is also selected from the group of high-risk patients, defined by the following criteria:

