no LAAC [DRG: F95A; OPS code 8-837.s0 (since 2016) or 8-837.s (before 2016)] procedure documented andtreatment with best medical care (NOACs (dabigatran (ATC code B01AE07), rivaroxaban (ATC code B01AF01), apixaban (ATC code B01AF02), edoxaban (ATC code B01AF03)) or VKA [phenprocoumon (ATC code B01AA04), and warfarin (ATC Code B01AA03)]For both groups, an additional exclusion criterion according to the CLOSURE-AF trial of a severe renal failure (ICD N18.5) or current requirement for dialysis (ICD Z49.1, Z49.2 in the quarter of inclusion) is applied (23).

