#### SHI data collection

2.3.2

SHI patient data are transferred for each year for the time period from 01.01.2015 to 31.12.2021; for each patient included, at least one year of baseline data (used to confirm inclusion/exclusion criteria prior to observation period) and at least two years of follow-up data are captured. The data include information on
sociodemographic characteristics (age, gender, and insurance period)outpatient medical care [diagnoses (ICD-10), quarter of diagnoses, procedures, costs of care]pharmaceuticals (dispensed drugs, numbers of packages, prescription date, dispense date, and costs of therapy)medical devices and allied health services (type of therapy or device, service provider, and therapy duration and costs)unemployability (diagnoses, sick leave durations and payments, and durations), andinpatient medical care: main and secondary diagnoses (ICD-10) upon discharge, surgeries and procedures (OPS), date and cause of admission, date and reason for discharge, and DRG code.

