### Outcome measures and analyses

2.4

The EvaClosure study design consists of four modules that build on one another (see Table 2). For module A1, a cost-of-illness study assesses direct and indirect costs associated with a high risk of stroke and bleeding in patients with AF. Focusing on the high-risk group only, module A2 compares direct and indirect costs associated with LAAC treatment to best medical care. Module B1 quantifies the utility effect of LAAC in terms of QALYs gained compared with standard of care via data of the EvaClosure study population. The subsequent module B2, on the other hand, combines SHI claims data and data from the EvaClosure study population as well as CLOSURE-AF trial results to conduct a cost–utility analysis.

**Table 2 T2:** Overview study modules, design, and outcome measures.

Module	Main Objectives	Study population	Design	Time frame	Costs/Outcomes
A1	To assess cost of illness to high-risk of stroke and bleeding in patients with AF	SHI study population, divided into the high-risk AF group and the AF group without high risk	Longitudinal cohort study, retrospective (difference-in-differences)	2015–2021; 1 year before and 4 years after inclusion per individual	direct and indirect costs
A2	To assess direct and indirect costs of LAAC intervention vs. best available medical care in high-risk patients with AF	EvaClosure study population: high-risk AF patients divided into intervention and control groups as per the CLOSURE-AF protocol.	Longitudinal cohort study, prospective (difference-in-differences)	2018–2025; enrollment starting in 01/2021 with a follow-up of up to 24 months	Direct and indirect costs
		SHI study population: the high-risk AF group divided into intervention and control groups as close as possible to the CLOSURE-AF protocol	Longitudinal cohort study, retrospective (difference-in-differences)	2015–2021; 1 year before and 4 years after inclusion per individual	
B1	To assess the utility effect of LAAC compared with best medical care	EvaClosure study population: high-risk AF patients divided into intervention and control groups as per the CLOSURE-AF protocol	Longitudinal cohort study, prospective	2018–2025; CLOSURE-AF enrollment starting in 03/2018; obtaining informed consent for prospective and retrospective participation in EvaClosure started in 01/2021, patient individual follow-up of up to 24 months	Health-related quality of life, QALYs

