Because of the reduced risks of stroke and bleeding and less need for lifelong medication, we can also assume that LAAC-treated patients report a less deteriorated or even better health-related quality of life in the medium and long term compared with the control group; in other words, assuming no negative effect on life expectancy, there is an expected gain in QALYs from two years after the intervention. If there is a less pronounced increase in costs, this would make LAAC a dominant stroke prevention strategy from both SHI and societal perspectives.

It is a well-known phenomenon that clinical study results may not fully reflect real-world care outside of tightly controlled conditions of clinical trials (52). Our approach of combining trial and real-world SHI data allows us to evaluate the cost-effectiveness of LAAC compared with best medical care [including (N)OAC therapy] but also in contrast to all high-risk AF patients, regardless of their individual (drug) therapy. This largely reflects the situation in the real world, where patients may not fit criteria for standard medication or may switch therapy, making the results particularly applicable to economic decisions in a real-world setting.

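### The claims control group excludes patients with a documented LAAC but sets no time window, so membership can depend on what happens after the index date, or one person can qualify for both groups

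*Protocol article*

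**What the plan says.** Section 2.3.1 (SHI study population) builds both claims groups from one high-risk pool. For the LAAC group: "From the high-risk patients, the LAAC intervention group is selected using the following inclusion criteria", followed by a DRG and an OPS code. A control must have "no LAAC [DRG: F95A; OPS code 8-837.s0 (since 2016) or 8-837.s (before 2016)] procedure documented" and be treated with one of the listed NOACs or VKAs. Neither rule states a period, and nothing is said about a patient who starts a listed drug and has LAAC later.

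Neighbouring criteria do carry a window. For high-risk status: "Patients are assigned to the high-risk group if in the baseline period they additionally have the following characteristics". For the dialysis exclusion: "current requirement for dialysis (ICD Z49.1, Z49.2 in the quarter of inclusion". Section 2.3.2 adds a general statement that each patient has "at least one year of baseline data (used to confirm inclusion/exclusion criteria prior to observation period".

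On the data span: "EvaClosure uses data from the years 2015 to 2021". Table 2 gives each claims patient one year before and four years after inclusion, and describes the A2 claims population as "the high-risk AF group divided into intervention and control groups as close as possible to the CLOSURE-AF protocol". Section 2.4.2 places the before/after split at the quarter of LAAC in one group and at the first listed drug in the other.

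**The concern.** Control time begins when a listed drug is first given. If a LAAC two or three years later cancels control status, the comparator is chosen partly on its own future. That future event is unlikely to be neutral: the Background names bleeding among the reasons for stopping anticoagulation and describes LAAC as an option when long-term anticoagulation is contraindicated. Matching on age, sex, comorbidity, risk scores and drug class cannot undo selection on a later event. Difference-in-differences cannot either, because the distortion lies in the post-index period.

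The control group supplies the A2 cost difference, through it the ICER, and the claims-based control risks for the Markov model (section 2.4.4). CLOSURE-AF, which the claims groups are meant to resemble, assigns groups by 1:1 randomisation, so membership there is fixed at entry and not by the absence of a later procedure.

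**Working it through.** The article gives no figure on this point. Its only calculation, the sample size in section 2.2.2, concerns the QALY comparison and is not affected. The check is therefore a reading of the rules, followed by a sensitivity range on stated assumptions.

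**1. Which window applies?** The baseline-year statement in section 2.3.2 would settle the matter if it governed every criterion. It cannot govern the LAAC codes uniformly. The same codes select the LAAC group, and for that group the LAAC quarter is itself the index. The codes must therefore be searched beyond the pre-index year, and the control rule reads as the mirror image of that search. Nor is baseline-only checking applied throughout: section 2.4.1 refers to bleeding-risk diagnoses in the observation period. The natural reading is no LAAC anywhere in the 2015 to 2021 data, but the text does not say so.

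**2. One patient under both readings.** Take a high-risk patient with baseline year 2016, a listed drug started early in 2017, a bleed in mid-2018 and LAAC early in 2019.
- No-window reading: the patient is not a control. With the DRG and OPS codes, the patient is a LAAC case indexed in 2019. The drug-treated time from 2017 leaves the comparator, and the bleed falls in the LAAC group's pre-period year.
- Baseline-only reading: 2016 shows no LAAC, so the patient is a control indexed in 2017. The patient also meets the LAAC criteria with index 2019. No rule assigns the patient to either group or allows for membership of both.

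**3. Size on the no-window reading.** Let c be the share of would-be controls who later have LAAC, and k their event or cost rate relative to the remaining controls, whose mean is m.
- Mean of all would-be controls: (1 − c)·m + c·k·m.
- Mean after removal: m.
- Ratio, restricted to full: 1 / ((1 − c) + c·k).

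The article gives neither c nor k; both are assumed.

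| c | k = 0.8 | k = 1 | k = 2 | k = 3 | k = 5 |
|---|---|---|---|---|---|
| 1% | 1.002 | 1.000 | 0.990 | 0.980 | 0.962 |
| 5% | 1.010 | 1.000 | 0.952 | 0.909 | 0.833 |
| 10% | 1.020 | 1.000 | 0.909 | 0.833 | 0.714 |

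Example: c = 5%, k = 3 gives 1 / (0.95 + 0.15) = 1 / 1.10 = 0.909, so the control mean is about 9% too low. For c from 1% to 10% and k from 2 to 5 the shortfall runs from 1 − 0.990 = 1% to 1 − 0.714 = 29%. At k = 1 there is no bias; below 1 it reverses slightly.

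**4. The A2 contrast.** The estimate is (post − pre) in the LAAC group minus (post − pre) in the control group. Removing costly crossovers lowers the control group's post-period mean and makes LAAC look dearer. A bleed in the LAAC group's pre-period raises that group's starting level and makes LAAC look cheaper. The net sign cannot be read from the article.

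**The case against.** The strongest reply is that the text never says the exclusion applies at any time, and that section 2.3.2 points to checking criteria before observation begins. A look-back window for one code is also something an article may leave to the full protocol. The first part stands as a caution: the no-window reading is an inference. It does not remove the point, because the baseline-only reading leaves overlapping groups. Nor is this an omitted detail: the selection rule is printed, with windows on its neighbours and none here.

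Four stronger readings are tempting and are not supported.
- A reader might infer that crossover patients disappear from the study. They leave the comparator, but those with the LAAC codes enter the LAAC group and their procedure is counted there.
- A reader might infer that control costs and bleeding risks are certainly too low. That requires above-average rates among crossovers. They must also survive to their LAAC, so removing them raises observed control mortality, which works the other way.
- A reader might infer that the ICER sets as-randomised QALYs against costs in patients who never crossed over. The article names no analysis set for module B1; Table 2 says only that the groups follow the CLOSURE-AF protocol.
- A reader might see a flat contradiction with the Discussion, which speaks of a real world "where patients may not fit criteria for standard medication or may switch therapy". That sentence follows a comparison with all high-risk patients whatever their drug therapy, and does not promise that the drug-treated control group keeps its crossovers.

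A partial safeguard also stands: sections 2.4.4 and 2.5 plan to adjust and re-run the Markov model with CLOSURE-AF results, so claims-based control risks are not its only source. This does not repair the A2 costs.

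**Conclusion.** The point holds as a defect in a stated selection rule. On the natural reading, control membership depends on an event after the index date that is plausibly related to the outcomes. On the alternative reading, the groups overlap without an assignment rule. Either can bias the A2 cost difference, the ICER built on it and the claims-based control risks.

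Neither direction nor size can be derived from the article. Control event risks would be too low if crossovers have above-average event rates; the range of about 1% to 29% rests wholly on assumed shares and rate ratios and ignores the matching weights. The crossover share can be counted directly in the claims, which would show whether the issue is negligible or material.

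**What to change.** Change the control criterion in section 2.3.1 to: no LAAC documented up to and including the index quarter. Then:
- Do not drop a control for a later LAAC. Keep that patient's control person-time and events up to the procedure.
- Report the control results twice: with these patients retained as first assigned, and with censoring at LAAC using inverse-probability-of-censoring weights.
- State how a person eligible for both groups is handled. One option is to match each LAAC patient, at the LAAC quarter, to controls who are still without LAAC at that time. Barring prior drug users from the LAAC group is not advisable: if LAAC often follows failed anticoagulation, it could remove much of that group.
- Report the number and share of controls with a later LAAC.

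The cost is a revised claims query, one extra analysis, and variance estimation that allows for persons contributing to both groups.

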The CLOSURE-AF-DZHK16 study addresses this research gap. CLOSURE-AF is a prospective, randomized clinical trial involving 42 study centers in Germany^1^ that analyzes the clinical benefit of LAAC in patients with non-valvular AF (NVAF) at high risk of stroke and bleeding (high-risk group)^2^ compared with best physician–directed medical care (including anticoagulation, when tolerated). Patient enrollment began in February 2018, with a study completion date in November 2024. Subjects were randomized 1:1 in the intervention and control group, receiving either catheter-interventional LAAC with a CE-certified LAA occluder (e.g., Watchman™, Amplatzer Amulet) or physician-directed best medical care [NOACs or vitamin K antagonists (VKA), antiplatelet therapy, no antithrombotic/antiplatelet therapy in case of contraindications] chosen at the discretion of the treating physician (23).

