Changing standard care by introducing a novel medical device must be supported by evidence of both clinical and economic benefits. However, evidence on LAAC cost-effectiveness in high-risk patients is lacking. Therefore, an incremental analysis of the costs and benefits of the intervention compared with standard medical therapy is essential to adequately reflect its utility for patients as well as the economic impact from the perspectives of both SHI and society. Previous health economic evaluations of LAAC (25–32) predominantly considered patients with NVAF without accounting for contraindications to (N)OACs. All but one of the eight studies evaluated LAAC cost-effectiveness based on incremental costs per quality-adjusted life year (QALY). Two out of the eight identified studies considered NVAF patients with contraindications, for which the results suggest that, depending on the time horizon, LAAC is cost-effective compared with therapy with apixaban or aspirin or represents the dominant treatment alternative for patients with AF at risk of stroke and contraindications to (N)OACs (30, 31). Based on health economic modeling, Reddy et al. (30) found that LAAC was more clinically effective and, after a time horizon of eight years, also more cost-effective in this high-risk group. However, none of the aforementioned studies compared LAAC treatment with a control group, where treatments are not limited to those specific medications. Such a restriction does not reflect real-world standard care, which is relevant for economic evaluation from the perspectives of both SHI and society. Moreover, in Germany, no health economic evaluation has yet been conducted for the—potentially particularly effective—clinical use of LAAC in this specific high-risk population recruited in the CLOSURE-AF trial.

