#### EvaClosure study population

2.2.1

The EvaClosure population comprises a subgroup of the CLOSURE-AF trial participants who consented to participate in the health economic evaluation (=EvaClosure study). Thus, the EvaClosure population includes both newly recruited patients and study participants who had already been enrolled in the CLOSURE-AF trial (see the section “trial data collection” for further details).

Patients enrolled in the CLOSURE-AF study do not have to meet any further criteria (apart from giving consent) to participate in the EvaClosure substudy. The eligibility criteria for CLOSURE-AF have been described elsewhere in detail (23); the trial includes patients 18 years or older with documented AF (paroxysmal, persistent, or permanent) and with high risk of bleeding or stroke. High risk of bleeding and stroke is determined by the CHA_2_DS_2_VASc and HAS-BLED scores as well as other characteristics [see (37, 38)]. Moreover, patients must be suitable candidates for catheter-interventional atrial appendage closure. Only those patients with an absolute contraindication to ASA and other antiplatelet drugs such as P2Y12-inhibitors like clopidogrel or with other comorbidities requiring long-term (N)OAC treatment were excluded from the study. Patients in the control group will be treated at the discretion of their local physician according to recommendations based on their specific bleeding risk. Patients will receive one of four approved NOAC treatments in different doses, including the relevant dose-reduction criteria: dabigatran, rivaroxaban, apixaban, or edoxaban. Table 1 summarizes the approved (N)OACs and doses. In case of contraindications to NOACs, patients may be either treated with vitamin-K antagonists (warfarin, phenprocoumon) and antiplatelet agents or there will be no stroke preventive treatment.

**Table 1 T1:** (N)OACs and approved/studied doses across indications.

(N)OACs	Higher dose	Lower dose
Dabigatran	150 mg BID (CrCl >30 mL/min)	110 mg BID [Age >80, Interacting drugs (e.g., verapamil), CrCl 15–30 mL/min]
Rivaroxaban	20 mg/d (CrCl >50 mL/min)	15 mg/d (CrCl 15-50 mL/min)
Apixaban	5 mg BID	2.5 mg BID (if two of the following present: age >80, weight <60 kg, serum creatinine >1.5 mg/dL)
Edoxaban	60 mg/d	30 mg/d (weight <60 kg, CrCl 15-50 mL/min)

BID = twice daily; CrCl, creatinine clearance.

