#### A2: direct and indirect costs in high-risk AF patients: LAAC procedure vs. best available medical care

2.4.2

To estimate direct and indirect costs, a population with maximum similarity to the EvaClosure study population will be selected from SHI claims data by statistical matching. Age, gender, comorbidity, CHA_2_DS_2_VASc and HAS-BLED scores, and medications (by classification) taken by control group patients will be used for matching of the populations, as observed by the quarter and year in which they and their statistical match meet the inclusion criteria. Matching will be verified using clinical trial data on medication, periprocedural events, (serious) adverse events, and comorbidities detected during follow-up visits of CLOSURE-AF trial patients. In the SHI population, healthcare costs of the LAAC group within a 2- and 5-year time frame will be estimated as the difference between the costs induced by the intervention group and the control group. Indirect costs will be evaluated based on the difference in the average length of incapacity to work documented per group, priced using industry-specific average employee compensation in Germany.

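### The claims-data control group admits only NOAC or VKA users while the trial control arm also holds antiplatelet-treated and untreated patients, so the ICER combines two different comparators

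*Protocol article*

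**What the plan says.** **Trial control arm.** The Background section of the Protocol article lists NOACs or VKA and then "antiplatelet therapy, no antithrombotic/antiplatelet therapy in case of contraindications] chosen at the discretion of the treating physician". The section on the EvaClosure study population says that, where NOACs are contraindicated, "patients may be either treated with vitamin-K antagonists (warfarin, phenprocoumon) and antiplatelet agents or there will be no stroke preventive treatment".

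**Claims control group.** The section on the SHI study population sets two joint conditions: no documented LAAC, and "best medical care (NOACs (dabigatran (ATC code B01AE07), rivaroxaban (ATC code B01AF01), apixaban (ATC code B01AF02), edoxaban (ATC code B01AF03)) or VKA", the VKAs being "phenprocoumon (ATC code B01AA04), and warfarin (ATC Code B01AA03". It lists no antiplatelet code and no untreated category.

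**Stated intention.** Table 2 says that the claims groups for module A2 should follow the CLOSURE-AF protocol as closely as possible. Of earlier evaluations, whose comparators were confined to particular drugs, the Background says: "Such a restriction does not reflect real-world standard care".

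**Matching and index.** Section A2 lists age, gender, comorbidity and the two risk scores, "and medications (by classification) taken by control group patients will be used for matching of the populations". For the before-and-after comparison, the control index quarter is that of the first treatment with one of the drugs defined as best medical treatment.

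**Use.** Section B2 builds the ICER from the A2 costs and the B1 QALYs. It also tunes the Markov transition probabilities on the matched claims groups.

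**The concern.** An ICER needs costs and effects for the same pair of strategies. Here the claims-based numerator sets LAAC against anticoagulated patients, while the denominator sets LAAC against whatever the treating physician chose, including no antithrombotic drug. The lifetime model has the same split, because control-arm event risks tuned on the claims groups come from anticoagulated patients. Patients with contraindications to anticoagulation are central to the study's stated rationale, and the claims control leaves out those who receive neither a NOAC nor a VKA. The limitations in the Discussion do not mention the difference.

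**Working it through.** The article gives no figure on this point. Its one sample-size calculation concerns the QALY comparison and is not involved. The check is a comparison of definitions, followed by the algebra of the effect.

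**1. Who can be a control**

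| Therapy of a high-risk patient without LAAC | Trial control arm | Claims control group |
|---|---|---|
| NOAC | yes | yes |
| VKA | yes | yes |
| Antiplatelet therapy only | yes (Background) | no |
| No antithrombotic therapy | yes (Background; EvaClosure study population) | no |

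The section on the EvaClosure population words the antiplatelet option less clearly, joining it to VKA. The Background lists it separately. Both allow untreated patients.

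**2. Can matching repair it?** No. If medication class is a matching variable, a trial control in the third or fourth row finds an empty cell. That patient is either dropped or paired with an anticoagulated person. In both cases the matched claims control consists wholly of NOAC or VKA users.

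**3. Can the index rule accommodate such patients?** No. A patient who never receives one of the listed drugs has no index quarter, so no before-and-after contrast exists.

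**4. Is the restriction symmetric?** No. The claims LAAC group is defined by DRG and OPS codes, without any drug requirement.

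**5. What happens to the ICER?** Let s be the share of trial controls without a NOAC or VKA. Let D be the before-to-after cost change in such patients minus that in NOAC or VKA users. The control change for the trial's mix is

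(1 − s) × change(OAC) + s × change(no OAC) = change(OAC) + s × D.

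The incremental cost against the trial's comparator is therefore the planned estimate minus s × D. The control transition probabilities shift in the same way, by s times the difference in risk. D is a difference in changes, because difference-in-differences removes stable differences in cost level.

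**6. Size.** Neither s nor D is in the article. For illustration only, assume s from 5% to 30% and D from 500 to 2,000 euros in absolute value. The shift then runs from 0.05 × 500 = 25 to 0.30 × 2,000 = 600 euros per patient, of unknown sign.

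**7. Related eligibility gap.** The trial is in non-valvular AF, and patients "or with other comorbidities requiring long-term (N)OAC treatment were excluded from the study". The claims criteria carry over the trial's renal exclusion but neither of these. Both claims arms come from the same pool, so the gap concerns both. Selecting controls by an OAC prescription may enrich such patients there.

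**The case against.** The strongest reply has five parts.

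- **Prescription data set limits.** Over-the-counter aspirin would not appear in claims, so antiplatelet-only and untreated patients cannot be told apart reliably. A prescription-based definition may be as close to the trial as the data allow. This stands against separating those two groups, but not against pooling them.
- **The ICER does not rest on claims costs alone.** FIMA data supplement them, the final model is adjusted to CLOSURE-AF results, and a sensitivity analysis addresses sample selection. These steps soften the mismatch. None changes the claims comparator.
- **The Discussion announces a contrast with all high-risk patients whatever their drug therapy.** It does, but no group or module in the Methods defines that contrast for LAAC.
- **The affected share may be small.** NOACs are the default in the trial, and some patients with contraindications receive a VKA and remain matchable. This stands: no share is given.
- **The Background criticises something narrower.** It objects to comparators limited to specific medications, whereas the claims control admits six agents in two classes. This also stands. The claims control is narrower than the trial arm, but it is not the identical restriction.

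A reader might also infer that the claims controls are all patients who tolerate anticoagulation, or that the sickest patients are the ones missing. The document supports neither. It requires treatment, not persistence, and itself puts first-year discontinuation or non-adherence at about 15% to 30%. Nor does it show that patients with valvular AF or another long-term OAC indication enter the control arm only.

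**Conclusion.** The point holds as a contradiction between definitions. The claims control is OAC only, the trial control is mixed, and B2 combines results from both in one ratio. This rests on the text of the article and needs no assumption about costs. It affects the claims-based part of A2, and B2 wherever claims costs or claims-derived risks enter. FIMA-based costs are untouched.

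A reader might want to attach a euro amount or say which strategy is favoured. The document supports neither: the share and the cost differences are absent, and a simple difference in annual cost level would not pass through difference-in-differences. The range in the working is an illustration of scale under assumed inputs.

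The omitted non-valvular and long-term OAC criteria are a secondary matter, with possible but unproven enrichment among controls. Because the ICER is the end product of the study and the remedy lies in cohort definitions, the mismatch should be resolved before the analysis.

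**What to change.** - Add to A2 and B2 a claims control of all high-risk patients without LAAC regardless of drug therapy, which is the contrast the Discussion announces.
- Split it into an OAC stratum and a no-OAC stratum, pooling antiplatelet-only and untreated patients. Weight the strata to the therapy mix of the trial control arm.
- Assign an index quarter that needs no OAC prescription, for example one matched to the calendar quarter and time since qualification of the LAAC patients, with high-risk status established in the preceding baseline period. This avoids giving untreated patients a different time zero from LAAC patients.
- Report the ICER with this comparator and with the present group, and label the latter as OAC only.
- Apply the non-valvular restriction and the exclusion of other long-term OAC indications to both claims arms, as far as codes allow.
- Reconcile the Background, SHI study population, A2 and Discussion sections, and name the difference among the limitations.

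**Cost.** This is a change of code lists and cohort definition. Module A1 already uses the whole high-risk group, and dispensed drugs are in the extract. The weighting needs the control-arm therapy mix from the trial. The no-OAC stratum may include people unsuitable for LAAC, whereas trial patients had to be suitable, so residual confounding has to be acknowledged.
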